## Abstract

**Background:**

Most acute stroke patients with disabilities do not receive recommended rehabilitation following discharge to the community. Functional and social barriers are common reasons for non-adherence to post-discharge rehabilitation. Home rehabilitation is an alternative to centre-based rehabilitation but is costlier. Tele-rehabilitation is a possible solution, allowing for remote supervision of rehabilitation and eliminating access barriers. The objective of the Singapore Tele-technology Aided Rehabilitation in Stroke (STARS) trial is to determine if a novel tele-rehabilitation intervention for the first three months after stroke admission improves functional recovery compared to usual care.

**Methods/design:**

This is a single blind (evaluator blinded), parallel, two-arm randomised controlled trial study design involving 100 recent stroke patients. The inclusion criteria are age ≥40 years, having caregiver support and recent stroke defined as stroke diagnosis within 4 weeks. Consenting participants will be randomized with varying block size of 4 or 6 assuming a 1:1 treatment allocation with the participating centre as the stratification factor. The baseline assessment will be done within 4 weeks of stroke onset, followed by follow-up assessments at 3 and 6 months. The tele-rehabilitation intervention lasts for 3 months and includes exercise 5-days-a-week using an iPad-based system that allows recording of daily exercise with video and sensor data and weekly video-conferencing with tele-therapists after data review. Those allocated to the control group will receive usual care. The primary outcome measure is improvement in life task’s social activity participation at three months as measured by the disability component of the Jette Late Life Functional and Disability Instrument (LLFDI). Secondary outcome variables consist of gait speed (Timed 5-Meter Walk Test) and endurance (Two-Minute Walk test), performance of basic activities of daily living (Shah-modified Barthel Index), balance confidence (Activities-Specific Balance Confidence Scale), patient self-reported health-related quality-of-life [Euro-QOL (EQ-5D)], health service utilization (Singapore Stroke Study Health Service Utilization Form) and caregiver reported stress (Zarit Caregiver Burden Inventory).

**Discussion:**

The goal of this trial is to provide evidence on the potential benefit and cost-effectiveness of this novel tele-rehabilitation programme which will guide health care decision-making and potentially improve performance of post-stroke community-based rehabilitation.

**Trial Registration:**

This trial protocol was registered under ClinicalTrials.gov on 18 July 2013 as study title “The Singapore Tele-technology Aided Rehabilitation in Stroke (STARS) Study” (ID: The STARS Study, ClinicalTrials.gov Identifier: NCT01905917).

## Background

Supervised therapy is an important factor in determining post-stroke functional recovery. In a 1-year cohort study on local post-stroke patients in the community, only a third of the subjects undergo supervised rehabilitation one month after discharge into the community [1]. Those who performed supervised therapy >25 % of the recommended amount of time recovered faster than those who performed a lesser amount of supervised therapy <25 % at 1- and 6-months. Performing therapy at outpatient rehabilitation centre at 1- and 6-months post-stroke is also independently predictive of better Barthel Index (BI) scores at 1 year (72.4 vs. 62.7 at 1 month and 74.7 vs. 59.4 at 6 months). Greater functional independence is associated with reduced caregiver burden, better patient health-related quality of life and potentially lower cost of care [2–5].

In a mixed methods study on non-adherence with recommendations for continued rehabilitation, although 86 % acknowledged that rehabilitation was beneficial, only 40 % intended to continue with rehabilitation after discharge, citing functional and social (e.g. unwillingness to inconvenience their caregiver) barriers [5]. Based on the qualitative results, a quantitative questionnaire was administered on a new set of 70 patients with follow-up telephone interviews at three, six, nine and twelve months after discharge. The longitudinal adherence to rehabilitation rate fell from 100 % in hospital to 20.3 % at 3 months, 9.8 % at 6 months, 6.3 % at 9 months and 4.3 % at 12 months after discharge.

Solutions to addressing non-adherence to rehabilitation include the use of transportation and mobility systems such as stair-lifts for stroke survivors living in apartments on floors without access to an elevator. Paid handicap-fitted transport services to ferry stroke survivors to and back from outpatient rehabilitation centers can also overcome physical barriers. Providing paid caregivers for social support and subsidies for outpatient rehabilitation may reduce financial and social barriers. Nevertheless, all such services and/or equipment are expensive; moreover, caregivers are in short supply around the world [5].

Given the heavy cost and inconvenience incurred in transporting stroke survivors to outpatient rehabilitation centers, home rehabilitation seems to be a viable option in the delivery of post-stroke recovery. Even through home rehabilitation was shown to be equally effective as inpatient rehabilitation [6, 7], it is less cost-efficient than outpatient rehabilitation center [5]. Gladman et al. randomized 327 patients to receive domiciliary or routine (hospital-based) care. Over a 14-month time frame, mean per patient costs for hospital-based services were less than domiciliary services [8]. Indeed, the cost of home rehabilitation is at least two times more expensive than therapy at an outpatient rehabilitation center (in Singapore, the norm cost of one hour of home rehabilitation is S$125 per hour and one hour of centre-based rehabilitation is S$50 per hour [5]). The relatively higher cost for home rehabilitation can be attributed to the greater economies of scale in outpatient rehabilitation as compared to home rehabilitation [8]. For instance, home therapists can only see one patient at a time whereas centre-based therapists can directly supervise the treatment of more than one patient at a time.

Recent studies focus on the use of home-based tele-health technologies to provide support and guidance by rehabilitation therapists at a distance, representing a novel potential approach for addressing the access to post-acute rehabilitation care problem for stroke survivors [9]. Tele-rehabilitation provides greater convenience to patients and families and encourages rehabilitation within the patient’s home. A study by Sanford et al. showed the feasibility of providing a multi-factorial, multidisciplinary individualized, home-based tele-rehabilitation intervention, demonstrating improved self-efficacy in mobility-impaired adults (n = 16) to the same degree as those who received supervised rehabilitation with physiotherapists and occupational therapists at outpatient rehabilitation centers (n = 16) [10]. These findings were corroborated and extended in two subsequent randomized clinical trials, with differing populations (stroke survivors and intensive care survivors) [11–13]. However, the intervention still require home visits and video-recordings by a therapy aide. Moreover, as video-recordings do not allow the collection of physical and sensor information from patients, this approach to tele-rehabilitation limits the therapists’ assessment of patient performance.

Given the current heterogeneity and room for improvements in solutions related to post-stroke rehabilitation, there is a need for well-designed intervention and rigorous trial to close the gap. The Singapore Tele-technology Aided Rehabilitation in Stroke (STARS) Study is a parallel, two-arm (intervention-control), single blind (evaluator-blind) randomised controlled trial to determine if a novel tele-rehabilitation intervention can improve functional recovery of post-stroke patients. For the tele-rehabilitation intervention arm of this study, the team developed small affordable lightweight wireless wearable sensors which can be strapped onto patients to allow real-time biofeedback and collection of sensor data from the sensors for subsequent transmission to patient’s rehabilitation team wirelessly via the internet. The sensor data is automatically summarized in chart form for quick review by therapist to allow them to prescribe further rehabilitation exercises remotely. The system also automatically allows the patient to self-record videos of them exercising which will also be transmitted to the therapist (termed ‘tele-therapist’) for review where needed, and allow patients and their therapists to communicate with each other using video-conferencing. The study’s primary hypothesis is that this novel tele-rehabilitation intervention during the first three months after stroke admission will result in greater functional recovery compared to usual care three months after stroke admission, as determined by the Jette Late Life Functional and Disability Instrument (LLFDI). Secondary hypotheses are that tele-rehabilitation intervention during the first three months after stroke admission will result in greater functional recovery as determined by gait speed, 2-min walk test and Shah modified Barthel Index, less health service utilization, greater contact time with therapist, better balance, better quality of life, less caregiver burden and be more cost-effective compared to usual care three months after stroke admission. Process measures in the form of a diary will be used to assess improved adherence in rehabilitation. Outcomes will also be assessed again at six months post-stroke to determine whether any improvement in outcomes is sustained in both groups.

## Methods/Design

### Ethical approval

All procedures conducted during this trial with human participants were carried out in compliance with institutional ethical standards. All research procedures were approved by an Institutional Review Board (IRB) at each participating site: Singapore General Hospital (SGH) from Centralised Institutional Review Board (CIRB Reference No. 2011/779/D), and Ang Mo Kio Thye Hua Kwan Hospital (AMKTHKH) from National University of Singapore (NUS) IRB (NUS IRB Reference Code 11–013) and accepted by the National Healthcare Group Domain Specific Review Board (DSRB). SGH is an acute hospital with an acute stroke unit and an inpatient rehabilitation unit, whereas AMKTHKH is an inpatient rehabilitation hospital.

### Study design

This is a parallel, two-arm (intervention-control), and single blind (evaluator-blind) randomised controlled trial of a novel home-based tele-rehabilitation intervention provided for 3 months after discharge for stroke admission compared with usual care. Prior to the study, a pilot study was done to test the procedures, interventions and assessments. Eligible participants are randomized to the intervention and control groups at baseline before discharge from the hospital. With regards to mean length of stay in hospital, Chen. et al. reported that patients admitted in local inpatient rehabilitation hospitals (e.g. AMKTHKH) for stroke stayed for 33 days [14]. In another study done by Ng. et al., in which 57.9 % of the participants were admitted to an acute hospital (e.g. SGH) for stroke, the mean length of stay for acute referring unit and inpatient rehabilitation unit were 14.5 and 21.5 days respectively [15]. The primary outcome, as is discussed in a later section, is the Jette Late Life Functional and Disability Instrument (LLFDI) which measures social activity participation in life tasks. The trial workflow is summarized in Fig. 1.

**Fig. 1 Fig1:**
[figure not shown]
STARS Trial Workflow Diagram

### Inclusion and exclusion criteria

#### Stroke diagnosis

Participants are individuals with recent onset of ischemic or hemorrhagic stroke. For purposes of inclusion in this study, a stroke is defined, according to the World Health Organization definition, as “a rapid onset event of vascular origin reflecting a focal disturbance of cerebral function, excluding isolated impairments of higher function and persisting longer than 24 h [16]”. Stroke diagnosis will be made by a clinician and/or supported by brain imaging.

#### Inclusion criteria

The inclusion criteria for the trial are as follows: (1) age ≥ 40 years, (2) recent stroke (defined as stroke diagnosis occurring within 4 weeks prior to admission into inpatient rehabilitation unit or hospital), (3) able to sit unsupported for 30 s, (4) able to stand on the non-paretic leg for >4 s, (5) able to walk at least 2 m with maximum of 1 person assisting, (6) able to follow a 2-step command, (7) living in the community before stroke and expected to be discharged home, (8) has a caregiver when the patient is doing the exercises for safety reasons, as the tele-therapist is not present when the patient is doing the exercise and a caregiver is needed to catch the patient if he/she should fall.

#### Exclusion criteria

The exclusion criteria for the trial are as follows: (1) has a pacemaker in-situ (because of possible interference of pacemakers by wireless electronic signals), (2) unable to ambulate at least 45 meters (150 feet) prior to stroke, or intermittent claudication while walking less than 200 meters (656 feet), (3) serious cardiac conditions (e.g. hospitalization for myocardial infarction or heart surgery within 3 months, history of severe congestive heart failure, serious and unstable cardiac arrhythmias, hypertrophic cardiomyopathy, severe aortic stenosis, angina or dyspnea at rest or during activities of daily living), (4) history of serious chronic obstructive pulmonary disease or oxygen dependence, (5) severe weight bearing pain, (6) pre-existing neurological disorders such as Parkinson’s disease, amyotrophic lateral sclerosis, multiple sclerosis or severe dementia, (7) history of major head trauma with severe residual deficits, (8) lower extremity amputation, (9) legal blindness or severe visual impairment, (10) severe uncontrolled psychiatric illness such as psychosis, schizophrenia or medication refractory depression (11) life expectancy less than three months, (12) severe arthritis or orthopedic problems that limit passive ranges of motion of lower extremity (e.g. knee flexion contracture of > 10°, knee flexion ROM < 90°, hip flexion contracture > 25°, and ankle plantar flexion contracture > 15°), (13) history of sustained alcoholism or drug abuse in the last six months, (14) hypertension with systolic blood pressure greater than 200 mmHg and diastolic blood pressure greater than 110 mmHg at rest, that cannot be medically controlled into the resting range of 180/100 mmHg.

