### Participant recruitment

Participants will be recruited from the inpatient rehabilitation unit of an acute hospital (i.e. SGH) and an inpatient rehabilitation hospital (i.e. AMKTHKH). Each site is expected to recruit approximately 50 participants (25 intervention and 25 controls).

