### Screening process

Recruitment will be initiated while the stroke patient is still in the hospital. The research assistant will first screen the medical records for current admissions and medical histories including the list of diseases and conditions at the hospital sites. Once potential patients are identified, the research assistant will approach them and provide information about the study, both in written and verbal form, only after they have indicated their interests. The research assistant has to review the inclusion and exclusion criteria of patients that cannot be determined through medical records.

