### Standardization

Research assistants and tele-therapists will receive training provided by the study coordinator. The research assistants will be trained in assessing the eligibility of potential participants, obtaining informed consent from participants, randomization process, STARS tele-rehabilitation intervention protocol, the use of tele-rehabilitation system from the patient user interface, patient education on the use of the tele-rehabilitation system (including provision of written instructions to the participant), obtaining outcome measures for both intervention and control groups and documenting the measures. On the other hand, the tele-therapists will be trained in the use of tele-rehabilitation system from the tele-therapist user interface, progression protocols and documenting patients’ progress.

Competency of the tele-therapists and research assistants in their respective responsibilities will be assessed by the study coordinator at the end of the training programme. 90 % competency prior to participating in the study must be attained. To avoid drift, maintenance of competency is important in a multi-site clinical trial. Re-assessment will be done by the study coordinator every 6 months during the study at both sites.

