#### Hardware component

The hardware component comprises of an iPad, two limb sensors, a heart rate and blood pressure monitoring set and chargers for these devices. A stable movable floor-mounted flexible iPad stand will be provided to allow easy positioning of iPad to video-record exercises performed by the patient. Engineering details on the tele-rehabilitation system infrastructure and the accuracy of the sensors have been published [18, 19]. Only basic details necessary to understand how the tele-rehabilitation system works are mentioned here.

The limb sensor node is used in the system to determine the orientation of the limb being exercised, which is in turn sent to iPad to determine the number of repetitions and range of motion. Each sensor node consists of an ATMEGA328 microprocessor embedded on a printed circuit Board with three motion sensors and attached to a Bluetooth module. The three motion sensors attached are: ITG3200 (gyroscope) and LSM303DLHC (accelerometer and magnetometer). The Bluetooth module, which is a BLE112-A low energy single mode module produced by Bluegiga tech, is required for wireless communication with iPad.

The data collected from these motion sensors are polled into ATMEGA328 microprocessor through a daisy-chained I^2^C connection. The microprocessor will perform sensor fusion which involves the fusion of data to a 4-dimensional quaternion orientation vector using the algorithm devised by Madgwick [20] to denote the orientation of the sensor with respect to gravity. This is followed by date and time stamping the orientation. The resulting date/time-stamped orientation data is transmitted to the iPad using Bluetooth 4.0 connection. The patient application in the iPad will analyze the data to determine the orientation of the two limb sensors. The orientation data in turn is used to calculate the angle of movement as performed by the participant.

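### Exclusion criterion 14 joins its systolic and diastolic limits with 'and', so uncontrolled severe elevation of one component alone does not exclude a patient

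*Protocol article*

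**What the plan says.** In the protocol article, Exclusion criteria, item 14 excludes "hypertension with systolic blood pressure greater than 200 mmHg and diastolic blood pressure greater than 110 mmHg at rest, that cannot be medically controlled". The sentence ends with the control target: the patient is barred if the pressure "cannot be medically controlled into the resting range of 180/100 mmHg". The criterion therefore holds two pairs of numbers, a trigger pair (200 systolic, 110 diastolic) and a control pair (180 systolic, 100 diastolic).

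No other inclusion or exclusion criterion sets a blood-pressure limit. Exclusion criterion 3 covers cardiac conditions only.

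Eligibility is applied by research assistants. Under Screening process, "The research assistant has to review the inclusion and exclusion criteria of patients that cannot be determined through medical records". Under Standardization, "The research assistants will be trained in assessing the eligibility of potential participants", they must pass a competency check, and "Re-assessment will be done by the study coordinator every 6 months during the study at both sites".

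**The concern.** Joined by *and*, the two triggers act together: a patient is excluded only if systolic pressure is above 200 mmHg and, at the same time, diastolic pressure is above 110 mmHg. Severe elevation of one component alone then excludes nobody, however high it is and however resistant to treatment.

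That does not fit the rest of the sentence. A control range given as 180/100 is failed when either number is too high. A trigger that needs both numbers to be high lets in patients who plainly fail the control target of the same criterion.

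What is at stake is participant safety and uniform screening at two sites. Participants have had a recent stroke, and those in the intervention arm exercise at home; the Inclusion criteria note that "the tele-therapist is not present when the patient is doing the exercise". The statistical properties of the trial are not at stake. Randomisation follows eligibility, so any patient admitted this way is equally likely to enter either arm.

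**Working it through.** The plan gives no figure to reproduce here. The check is one of logic, run on example resting pressures that treatment has not lowered.

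**Inputs**, all from exclusion criterion 14: systolic trigger above 200 mmHg; diastolic trigger above 110 mmHg; control range 180/100 mmHg, read as systolic at most 180 and diastolic at most 100.

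**Rules compared**

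- As written: excluded if (systolic > 200 *and* diastolic > 110) and the pressure cannot be brought into the control range.
- Reworded: excluded if (systolic > 200 *or* diastolic > 110) and the pressure cannot be brought into the control range.

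**Results**

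| Uncontrolled resting reading (mmHg) | Within 180/100? | As written | Reworded |
|---|---|---|---|
| 215/95 | no | not excluded | excluded |
| 175/115 | no | not excluded | excluded |
| 240/110 | no | not excluded | excluded |
| 201/111 | no | excluded | excluded |
| 215/115 | no | excluded | excluded |
| 190/105 | no | not excluded | not excluded |
| 175/95 | yes | not excluded | not excluded |

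**Distance from the limits, for the three readings on which the rules differ**

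- 215/95: systolic is 215 − 200 = 15 above its trigger and 215 − 180 = 35 above the control limit.
- 175/115: diastolic is 115 − 110 = 5 above its trigger and 115 − 100 = 15 above the control limit.
- 240/110: systolic is 240 − 200 = 40 above its trigger and 240 − 180 = 60 above the control limit.

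The literal rule also orders patients oddly. With diastolic pressure at 110 or below, no systolic value excludes. So 240/110 passes, while 201/111, which is 39 mmHg lower in systolic and only 1 mmHg higher in diastolic pressure, is excluded.

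The readings are illustrative and say nothing about how often such patients occur.

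**The case against.** The best counter-argument is that *and* may simply list two limits, each sufficient by itself. Exclusion criterion 12 uses *and* that way: it closes a list of joint contractures that are clearly not all required together. The paired control range also points a sensible reader to the intended meaning, and screeners are trained, tested and re-assessed. This has some force. That *or* was intended is an inference, and the staff may already apply it. But criterion 12 uses the word inside a list of examples, whereas criterion 14 is the operative rule, and other criteria in the same list (2, 4 and 9) use *or* where one condition is enough. Nothing in the article says that one raised component suffices.

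A second objection is that the control range proves too much as a yardstick. An uncontrolled 190/105 also fails 180/100, yet it stays eligible under the reworded rule. That is correct. It follows from the gap between the control pair and the trigger pair, which is a separate choice of levels and is not challenged here. The rewording does not close that gap.

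Third, other protections exist. Under Participant recruitment, "Participants will be recruited from the inpatient rehabilitation unit of an acute hospital" or from an inpatient rehabilitation hospital, so candidates are under hospital care when screened. A caregiver must be present during exercise; the remark about the tele-therapist's absence was made to explain that requirement, as a guard against falls, and concerns the intervention arm only. The home equipment includes "a heart rate and blood pressure monitoring set and chargers for these devices". The tele-therapist assesses the patient before raising the difficulty, and intervention patients may also attend centre-based rehabilitation. These lower the risk, but none is a blood-pressure limit for entry.

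Finally, no wrongly enrolled patient is shown, and an inpatient awaiting discharge home with an uncontrolled 240/110 would be unusual. This bears on the severity of the point; the sentence still reads as it does.

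**Conclusion.** The point holds as a minor error of wording. As written, criterion 14 does not exclude uncontrolled 215/95, 175/115 or 240/110 mmHg, all of which fail its own control range.

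The literal effect is certain. That *or* was meant rests on inference from the paired control range. The conclusion assumes that 180/100 means both components at or below those values, and that a screener applies the text as it stands. How many patients are affected cannot be derived from the document; the number is probably small. Sample size, power, alpha and the comparison between arms are unaffected.

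**What to change.** Replace *and* with *or* and keep all four numbers. For example: *resting systolic pressure above 200 mmHg, or resting diastolic pressure above 110 mmHg, that treatment cannot bring down to 180/100 mmHg or below*.

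There are two routes. A formal amendment would go to the review boards of the two sites, for a trial that was already under way in July 2014 (Usual care). A screening clarification sent to both sites is lighter and can be covered at the existing six-monthly re-assessment of the research assistants. Neither needs a new measurement. The only foreseeable cost is possibly a few more screen failures, a number the document does not allow one to estimate.
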